#### **8.1.2. Secondary endpoints:**

The secondary endpoints are:

The effect will be analysed of the soluble fibre and consuming soluble fibre and a statin on:

- *The total cholesterol, the triglycerides, the HDL cholesterol, the apolipoproteins (apo) B-100 and A-1 and the lipoprotein (a).*
- *The oxidation markers: alpha tocopherol and gamma tocopherol in LDL, resistance of LDL to oxidation (lag time), LDL oxidation "in vivo" and lipid lipoperoxides.*
- *The inflammation markers: IL-1beta, interleukin-6, TNF-alpha, amyloid-A, high sensitivity C-reactive protein, fibrinogen, leukocytes.*
- *The indicators of antithrombotic activity: folic acid, homocysteine, plasminogen activator inhibitor (PAI-1).*
- *The individual response to the plasma lipids and their modulation by apolipoprotein E polymorphisms, cholesterol ester transport protein (CETP), apolipoprotein A-V, FABP 2, ABCG5 and ABCG8, fibrinogen, fibrinogen activator inhibitor, angiotensin converting enzyme and other polymorphisms which might describe their involvement in the development of cardiovascular diseases.*
- *Fasting complement component 3 (C3)*

- Mannose-binding lectin (MBL) activity
- Remnant-like particle cholesterol concentration (RLP-C)
- Parameters of cholesterol absorption and synthesis: plant sterols (campesterol and beta-sitosterol, reflecting cholesterol absorption) and lathosterol (reflecting cholesterol synthesis)
  - Determination of atherogenic apo B-containing particles (VLDL, IDL and LDL subclasses),
- HDL particle phenotype and HDL particle composition
- Cholesterol ester transfer protein activity

## **8.2. Trial Development**

See Annex 1 and 2

The study design is described schematically below:

- Inclusion period: Week –2 (D–15) , D-10 and D-7 (D-5)
- Randomisation and initiation of the intervention: Week 0 (S0).
- End of the 1st intervention period: Week 8 (S8).
- Beginning of 2nd intervention period (fibre + statin): from week 8 (S8)
- End of the 2nd intervention period: Week 16 (S16)

### **Visit schedule:**

#### **Visit S -2 (Day -15)**

The visits will include several aspects:

- Clinical
- Analytical
- Dietary

#### ➤ Clinical

Contact will have been made with all the possible participants from the centres for the systematic control of people in whom hypercholesterolemia has been detected. Similarly, patients from the lipid clinic of each centre will have been contacted.

Contact will be by a letter and/or by telephone call explaining the detailed contents on the **Patient Information Sheet**. (Annex 3)

Patients who agree to participate in the study will be invited to this initial visit to confirm that they meet the selection criteria. They will be given the patient information sheet and they will be invited to sign the informed consent form (Annex 4) for their participation in the trial.

At this visit a detailed clinical history will be made, particularly with regard to:

- Age
- Smoking
- Intake of alcohol
- Blood pressure
- Background of cardiovascular disease
- Concomitant diseases: diabetes mellitus, renal failure, serious acute infectious diseases, neoplasm, severe liver failure, chronic respiratory failure or associated endocrine diseases.
- Concomitant pharmacological treatments.
- Physical activity.
- The patient's diet

The physical activity of each participant will be assessed according to a specific questionnaire (Annex 5).

The physical examination will include the determination of blood pressure, weight, height, BMI and waist size.

The participant's weight will be determined: on one occasion the patient will get off the scales and will then be reweighed; the mean value of the 2 weighings will be calculated.

The height of the patient will be measured in the following way: the subject will breathe in and the height meter will be lowered to determine height. The measurement will be repeated and the mean value of the 2 measurements will be calculated.

Patients that comply with the selection criteria will be given the Patient Information Sheet and will be asked to **sign the Informed Consent Form** (Annex 4) to participate in the trial.

#### | *Analytical*

The patient will be given the blood test request form for extractions on days D –10 ( $\pm 2$ ) and D –7 ( $\pm 2$ ). The mean lipid profile will be calculated from these two blood tests and will be used as the baseline LDL-C value. The results should be available to the investigator at visit S0 to confirm that the patient complies with the analytical inclusion criteria. The analyses on the D-7 will be taken as the baseline for general haematological and biochemistry parameters. The genetic polymorphisms of this sample will also be analysed.

#### | *Dietary*

Each patient will be given a diet record for 3 days, two working days and one holiday, which they will complete and return at visit D-7. The patients will be instructed on how

to complete the record as precisely as possible, as indicated in the methodology section.

The patients will return the diet record on the day of the second analysis, i.e. D-7 ( $\pm 2$ ).

The dietician will have 7 – 10 days to analyse the data in the diet record and calculate patient energy requirements. He or she will thus be able to design the isocaloric diets for each case, which will be given to the patients at visit S0.

### **Visit S0**

This visit will be made no later than 9 days ( $7 \pm 2$ ) as of the date of the last blood sample extraction.

The visit will include several aspects:

- Clinical
- Analytical
- Dietary
  
- *Medication*

#### ➤ *Clinical*

A clinical history similar to that of S-2 will be made to confirm compliance with the inclusion criteria

Blood pressure and weight and height will be measured to calculate BMI at the physical examination.

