#### **Secondary endpoint**

- To study the combined cholesterol-lowering effect of treatment with *Plantago ovata* husk and statins to achieve the therapeutic objective.
- To analyse the effect of *Plantago ovata* husk fibre on blood pressure.
- To study the effect of the combination of statins with *Plantago ovata* husk on blood pressure.
- To evaluate whether the response on plasma lipids is modulated by the polymorphisms of apolipoprotein E, cholesterol ester transfer protein (CETP), apolipoprotein A-V and FABP 2.
- Furthermore, possible variations of the effects of the soluble fibre and the statins according to the characteristics at the beginning of the study, LDL-C level, gender or BMI will be studied.

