**Visit S4 (Day 28± 3)**

The participants will go to the Hospital and the visit will comprise several aspects:

➤ *Clinical*

Identify the presence of clinical problems, concomitant treatments, etc.  
Collection of adverse events

Blood pressure and weight will be taken.

➤ *Analytical*

A request for two analyses will be issued. For the blood extractions, the patient will go to the hospital during the week prior to visit S8 on two occasions, with a 3- or 4-day interval between them, and the last extraction will be performed at most 3 days before the following visit. In this way, the investigator will have both results, particularly for the lipid profile, at the S8 day visit.

Only the lipid profile will be determined at the first extraction. At the second extraction, and besides the lipid profile, the same biochemistry and haematological parameters as at visit S0 will be requested. Genetic polymorphisms will not be determined.

➤ *Dietary*

The patient will return the diet record delivered at week S0.

A new 3-day diet record to be returned at the following visit will be provided. (S8).

➤ *Medication*

Evaluate compliance with treatment with fibre. The patient should return used and unused medication containers.

The investigator will deliver the medication for the following treatment period until the next visit in week 8.

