### 12.3.2 Secondary efficacy analysis.

The combined cholesterol-lowering effect of treatment with *Plantago ovata husk* and statins to achieve the therapeutic objective will be studied. The proportion of successes, i.e. the patients in whom plasma LDL-C concentrations are below 130 mg/dl following combined treatment of *Plantago ovata husk* and statins will be calculated for each treatment.

The significance of the differences between these proportions will be evaluated using the chi-squares test. The null hypothesis considered will be that the proportion of success is the same in the two treatments for a two-tailed significance level of 0.05.

The effect of the treatment of *Plantago ovata* husk fibre on blood pressure will be evaluated by analytical procedures equivalent to those conducted to evaluate the effect of *Plantago ovata* husk fibre on plasma LDL-C concentration.

The effect of the combination of statins with *Plantago ovata* husk on blood pressure will be evaluated by analytical procedures equivalent to those conducted to evaluate the effect of the combination of statins and *Plantago ovata* husk on plasma LDL-C concentration.

The effect of the polymorphisms of apolipoprotein E, the cholesterol ester transfer protein (CETP), apolipoprotein A-V and the FABP 2 on the response in plasma lipid concentrations will be made by adjusting multiple regression models over the difference in plasma LDL-C concentrations between visits.

Furthermore, possible variations in the effects of the soluble fibre and the statins according to the characteristics at the beginning of the study, LDL-C level, gender or BMI will be studied.

A multiple linear regression model will be adjusted over the difference in the plasma LDL-C concentrations between visit S8 and visit S0, where the treatment carried out and the endpoints of age, gender, BMI, or LDL-C level at visit S0 will be used as covariates.

A multiple linear regression model will be adjusted over the success proportion, i.e. patients in whom plasma LDL-C concentrations are below 130 mg/dl following the combined treatment of *Plantago ovata* husk and statins, where the treatment carried out and the endpoints of age, gender, BMI or level of LDL-C at visit S0 will be used as covariates.

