# **ANNEX 1**

## **Study evaluations diagram**

## STUDY EVALUATIONS DIAGRAM VISITS

| Day / Week                      | S-2 | D-10 | D-7 | S0 | S4 | S7
(1) | S7
(2) | S8 | S12 | S15
(1) | S15
(2) | S16 |
|---------------------------------|-----|------|-----|----|----|-----------|-----------|----|-----|------------|------------|-----|
| Clinical history                | X   |      |     | X  | X  |           |           | X  | X   |            |            | X   |
| Physical Examin.                | X   |      |     | X  | X  |           |           | X  | X   |            |            | X   |
| Weight                          | X   |      |     | X  | X  |           |           | X  | X   |            |            | X   |
| Height                          | X   |      |     |    |    |           |           |    |     |            |            |     |
| BMI                             | X   |      |     | X  |    |           |           | X  |     |            |            | X   |
| Blood Pressure                  | X   |      |     | X  | X  |           |           | X  | X   |            |            | X   |
| Assessment
Physical Activity | X   |      |     |    |    |           |           | X  |     |            |            | X   |
| Informed
Consent             | X   |      |     |    |    |           |           |    |     |            |            |     |
| Lipid profile                   |     | X    | X   |    |    | X         | X         |    |     | X          | X          |     |
| Genetic
polymorphisms        |     |      | X   |    |    |           |           |    |     |            |            |     |
| Biochemistry                    |     |      | X   |    |    |           | X         |    |     |            | X          |     |
| Haemogram                       |     |      | X   |    |    |           | X         |    |     |            | X          |     |
| Minerals                        |     |      | X   |    |    |           | X         |    |     |            | X          |     |
| Vitamins                        |     |      | X   |    |    |           | X         |    |     |            | X          |     |
| Delivery of
diet record      | X   |      |     | X  | X  |           |           | X  | X   |            |            |     |
| Collection of
diet record    |     |      | X   |    | X  |           | X         |    | X   |            | X          |     |

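### The fibre-phase blood-pressure analysis defines no baseline and gives the untreated S-2 reading no role; using both pre-treatment readings would gain precision at no data cost

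*Protocol*

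**What the plan says.** **Objective.** Section 4.2 lists two blood-pressure aims among the secondary ones. One concerns fibre alone ("husk fibre on blood pressure"); the other begins "To study the effect of the combination of statins with" and concerns fibre with a statin.

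**Data collected.** At S-2 the protocol states: "The physical examination will include the determination of blood pressure, weight, height, BMI and waist size". At S0: "Blood pressure and weight and height will be measured to calculate BMI at the physical examination". At S4, and in the same terms at S8, S12 and S16: "Blood pressure and weight will be taken". The "Blood Pressure" row of Annex 1 marks S-2, S0, S4, S8, S12 and S16. S-2 (day -15) and S0 both precede treatment, because medication is first issued at S0. Both also precede the stricter saturated-fat limit that section 8.3.2 applies after randomisation.

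**Analysis.** Section 12.3.2 says that the fibre effect "on blood pressure will be evaluated by analytical procedures equivalent to those conducted to evaluate the effect of" fibre on LDL-C. Section 12.3.1 also lists blood pressure among the continuous secondary endpoints to be handled by an analogous ANCOVA. That model takes the S8 minus S0 difference as outcome and the baseline value as covariate.

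**Baseline.** For LDL-C, section 8.2 defines the baseline as the mean of the D-10 and D-7 tests, and that mean is recorded at S0. Nothing comparable is written for blood pressure, and no section says what the S-2 reading is for in the analysis.

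**The concern.** The LDL-C model carries over to blood pressure, but the two-determination baseline that goes with it does not. Read as written, the blood-pressure covariate is the S0 visit value alone, while an equally untreated value from about two weeks earlier sits in the database.

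A baseline covariate earns its place by predicting the final value. Visit-to-visit variation in one visit's blood pressure dilutes that prediction, and a second pre-treatment value recovers part of it. Section 4.1 describes the effect of fibre on blood pressure as moderate and says there are no data for this product. The endpoint is therefore one where precision matters, and the trial was not sized for it. What is at stake is some avoidable loss of power for a named secondary objective.

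**Working it through.** **Plan's own figure.** There is none to reproduce. The protocol gives no blood-pressure SD, correlation, effect size or power.

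**Inputs**
- One final reading (S8), with one pre-treatment reading (S0) or two (S-2 and S0): section 8.2 and Annex 1.
- Two-sided 0.05: section 12.3.1. Power 80%: borrowed from the LDL-C calculation in section 6.3.
- 145 randomised per arm: section 6.3. Less an assumed 15% losses: 145 × 0.85 ≈ 123 per arm.
- Between-visit correlation ρ: not in the documents. Assumed 0.4 to 0.8, equal for all pairs of visits.

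**Formulas** (blood-pressure variance set to 1)
- Residual variance with S0 only: 1 − ρ²
- Residual variance with S-2 and S0: 1 − 2ρ²/(1 + ρ)
- Detectable difference in SD units: (1.960 + 0.842) × √(residual variance × 2/123)

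| ρ | S0 only | S-2 and S0 | Variance cut | Detectable difference |
|---|---|---|---|---|
| 0.4 | 0.840 | 0.771 | 8.2% | 0.327 → 0.314 |
| 0.5 | 0.750 | 0.667 | 11.1% | 0.309 → 0.292 |
| 0.6 | 0.640 | 0.550 | 14.1% | 0.286 → 0.265 |
| 0.7 | 0.510 | 0.424 | 17.0% | 0.255 → 0.232 |
| 0.8 | 0.360 | 0.289 | 19.8% | 0.214 → 0.192 |

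The detectable difference scales with the square root of the variance. It shrinks by 1 − √(1 − 0.082) ≈ 4% at ρ = 0.4 and by 1 − √(1 − 0.198) ≈ 10% at ρ = 0.8.

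**Cross-check in mmHg.** Assume a between-person SD of 15, a within-person visit-to-visit SD of 8 and an SD of true change of 5, giving variances 225, 64 and 25.
- Variance of the final reading: 225 + 64 + 25 = 314.
- One baseline reading: 314 − 225²/(225 + 64) = 138.8.
- Mean of two: 314 − 225²/(225 + 32) = 117.0.
- Reduction: 1 − 117.0/138.8 = 15.7%.

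Over SDs of 12–15, 6–10 and 0–8 the reduction runs from 9.8% to 21.4%, in line with the table.

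**Mean or two covariates?** The table treats S-2 and S0 as equally informative. Suppose instead that S8 correlates 0.7 with S0 but only 0.5 with S-2, and that S-2 and S0 correlate 0.6 (all assumed).
- S0 alone: 1 − 0.7² = 0.51.
- Mean of the two: 1 − (0.7 + 0.5)²/(2 × 1.6) = 0.55, worse than S0 alone.
- Two separate covariates: 1 − (0.49 + 0.25 − 2 × 0.7 × 0.5 × 0.6)/(1 − 0.36) = 0.50.

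Two covariates cost one degree of freedom and do not rely on the visits being exchangeable. The mean gives the tabled gain only if they roughly are.

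**The case against.** **The baseline rule belongs in the SAP.** How several screening readings form a secondary baseline is often settled there, and the SAP is not shown. A procedure equivalent to that for LDL-C might even be read as allowing averaging, since the LDL-C value recorded at S0 is itself a mean. This stands as a reason not to call the protocol wrong. It does not remove the point, because the protocol names the S0 to S8 contrast, defines a two-test baseline for LDL-C and leaves blood pressure without one.

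**S-2 is the screening visit.** High blood pressure is one of the qualifying risk factors in section 6, so regression to the mean and habituation would fall most heavily on S-2. This is fair, and it favours two covariates over a mean. It does not create a difference between randomised arms. Section 6 also does not say that one study reading establishes the risk factor.

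**The gain is modest and rests on assumptions.** This stands. Blood pressure is one of many secondary endpoints, and no figure for it is given.

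**Stronger readings that the protocol does not support**
- *That blood pressure is a single, uncontrolled reading.* The visit text says it is determined, measured or taken, never how often or under what conditions. The case report form is attached separately and not shown. Silence is not a statement that one reading is taken.
- *That weight and height set a two-measurement standard for every visit.* The rule that "the mean value of the 2 weighings will be calculated", and its counterpart for height, are written for S-2 only.
- *That blood pressure deserved replication more than LDL-C.* LDL-C is the primary endpoint and also drives eligibility and the S8 decision, which explains its paired tests.
- *That the same baseline problem affects the statin phase.* Section 12.3.1 measures LDL-C change there from week 8 to week 16, so S0 is not the reference.

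**Conclusion.** The point holds as a low-cost improvement to the fibre-phase blood-pressure analysis. The inherited ANCOVA has no defined blood-pressure baseline, and a collected untreated reading is given no role. Using both readings would cut residual variance by about 8% to 20%, making the detectable difference about 4% to 10% smaller. These figures assume between-visit correlations of 0.4 to 0.8, equal across visits, with one final value per patient.

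A reader might infer that the present plan biases the blood-pressure comparison. It does not: in a randomised, double-blind comparison, noise in a baseline covariate costs precision and does not shift the contrast between arms.

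**What to change.** In section 12.3, state that the fibre-phase (S0 to S8) blood-pressure ANCOVA uses both pre-treatment readings, in one of two forms.

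1. **Two covariates (safer).** Enter the S-2 and S0 values separately. With S0 in the model, the estimated treatment effect is the same whether the outcome is the S8 value or S8 minus S0.
2. **Mean of S-2 and S0.** Use that mean both as the covariate and as the value subtracted from S8. Subtracting S0 while adjusting only for the mean would mix two definitions of baseline.

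Choose the form before unblinding. The cost is one sentence of analysis text, with no new visits, measurements or data fields. The week 8 to 16 analysis needs no change for this point.

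Separately and optionally, section 8.2 or 8.3 could state how many blood-pressure readings are taken per visit and under what conditions. That is a clarification, and the gain above does not depend on it.

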#### ➤ *Analytical*

The results of the mean LDL-C value obtained in the two analyses made on D-10 and D-7 will be noted. Similarly, the values obtained in the analysis on D-7 will be noted as baseline biochemistry and haematological parameters.

Furthermore, each patient's genetic polymorphism results will be collected at this visit.

#### ➤ *Dietary*

On the basis of the detailed analysis of the record returned by the patient on D-7 and the calculation of the energy needs (according to the Harris-Benedict formula), the patient will be assigned to one of the different diet energy levels, depending on their needs (From 1600 to 3100 Kcal daily): 1600, 1800, 2000, 2200, 2500, 2800 and 3100 Kcal.

The patients will talk about the diet record they completed during the selection phase with the dietician.

Each patient will be given a diet record for 3 days, two working days and one holiday, which they will complete and return at the next visit (S4) (Annex 6). Furthermore, they will be reminded of the instructions on how to complete the record as precisely as possible, as indicated in the methodology section.

➤ *Medication*

The medication necessary for the period from S0 until the next visit in S4 will be issued according to the randomisation number assigned. The patient will be informed as to when to take it and how to return it.

**Visit S4 (Day 28± 3)**

The participants will go to the Hospital and the visit will comprise several aspects:

➤ *Clinical*

Identify the presence of clinical problems, concomitant treatments, etc.  
Collection of adverse events

Blood pressure and weight will be taken.

➤ *Analytical*

A request for two analyses will be issued. For the blood extractions, the patient will go to the hospital during the week prior to visit S8 on two occasions, with a 3- or 4-day interval between them, and the last extraction will be performed at most 3 days before the following visit. In this way, the investigator will have both results, particularly for the lipid profile, at the S8 day visit.

Only the lipid profile will be determined at the first extraction. At the second extraction, and besides the lipid profile, the same biochemistry and haematological parameters as at visit S0 will be requested. Genetic polymorphisms will not be determined.

➤ *Dietary*

The patient will return the diet record delivered at week S0.

A new 3-day diet record to be returned at the following visit will be provided. (S8).

➤ *Medication*

Evaluate compliance with treatment with fibre. The patient should return used and unused medication containers.

The investigator will deliver the medication for the following treatment period until the next visit in week 8.

### **Visit S8 (Day 56± 3)**

The participants will go to the hospital for a visit addressing the following aspects:

➤ *Clinical*

A clinical history similar to that of S0 will be made

Identify the presence of clinical problems, concomitant treatments, etc.

Collection of adverse events.

Blood pressure and weight will be taken.

➤ *Analytical*

The results of the mean LDL-C value obtained in the two analyses made in the previous week (S7), at most 3 days before visit S8, will be noted. Similarly, the values obtained in the analyses on the last day of S7 will be noted as final parameters of the biochemistry and haematological trial.

➤ *Dietary*

The patients will already have returned the 3-day record the day they went to the hospital for the second blood sample extraction.

The dietician will address the diet follow-up and possible deviations. If the patient has to continue in the study he/she will be given diet guidelines according to his energy needs.

➤ *Medication*

Evaluate compliance with treatment with fibre. The patient should return used and unused medication containers.

**Two situations may arise at this point: 1) The patient has reached the therapeutic objective (LDL-C < 130) and will end the study, or 2) the patient will present an LDL-C ≥ 130 mg/dl and will continue with the same treatment with a statin (Simvastatin) added for a further 8 weeks.**

**The instructions on how to administer the fibre, the Simvastatin and, as the case may be, the patient's regular medication will be gone over once again.**

If the patient is to continue in the trial, the investigator will issue the same medication that the patient was taking + a statin in sufficient quantity for 4 weeks until visit S12.

